## Abstract

Rheumatoid arthritis (RA) is a chronic autoimmune disease that primarily affects cartilage and bone. Psychological stress can both trigger disease exacerbation and result from disease activity. As standard pharmacological interventions alone have limited success in treating RA, a more comprehensive biopsychosocial approach to treatment has been recommended. In this prospective randomized controlled trial (RCT), a psychotherapeutically guided, group-based intervention program will be conducted with RA patients over a period of 9 months. This program combines a dynamic-interactional model with disorder-specific coping-oriented perspectives to improve patients’ social, emotional, and problem-solving competencies as well as stress system functional status. The enrolment of 440 patients, randomly allocated to either an intervention (*n* = 220) or control group (*n* = 220), is planned. To evaluate the intervention effect, various indicators of RA disease activity, stress system activity, and psychological condition will be assessed through sets of standardized questionnaires and biochemical analyses of blood and saliva samples. Moreover, healthcare-related costs for each patient will be obtained using routine health insurance data. Outcome variables will be measured in all patients at regular intervals prior to intervention (baseline), during the 9-month intervention (five time points), and during a 9-month follow-up phase (three time points), allowing the comprehensive analysis of within- and between-subject effects, i.e. trajectories of the target variables in the intervention and control groups. In addition, to investigate the intervention effects on real-life stress system functioning in RA, 10 integrative single-case studies (*n* = 5 from the intervention group, *n* = 5 from the control group) will be conducted. In each study, once before and after the 9-month intervention, urine samples will be collected, and patients will fill out questionnaires for approximately 1 month at 12-h intervals. Moreover, weekly in-depth interviews will be conducted with patients to determine their previous week’s emotionally positive and negative incidents. Using time series analysis, it is then possible to investigate whether and how stress system function in these RA patients has improved from the applied intervention. By using both an investigational macro- and microperspective, this project aims to evaluate a psychological intervention in the routine care of individuals with RA.

**Trial registration** German Clinical Trials Register DRKS00028144. Registered on 1 March 2022.

## Background

Rheumatoid arthritis (RA) is an autoimmune disorder of connective tissue that usually follows a chronic course with characteristic destruction of cartilage and bone but can also present extra-articular manifestations (e.g. skin, eyes, lungs, heart, blood vessels) [1]. The clinical onset of RA often manifests as inflammation in the synovium of the hand and finger joints. However, as the disease progresses, more joints throughout the body become affected leading patients to report high levels of disease burden due to pain and restrictions in movement [2]. Additionally, there is a high comorbidity with psychiatric disorders, with depression being the most commonly observed condition [3, 4]. Despite state-of-the-art pharmacological interventions in form of disease-modifying antirheumatic drugs (DMARDs), many RA patients still experience various physical and psychological symptoms [5]. This indicates the need for novel therapeutic and supportive strategies.

This is where the field of psychoneuroimmunology (PNI) becomes relevant. PNI integrates psychological, neuroendocrinological, and immunological factors in addressing health and disease. In addition to other influences (e.g. genetic aspects, chronic infections, sex hormones), psychosocial stressors have frequently been identified as a risk factor in RA, i.e. triggering the onset of the disease and the occurrence of flare-ups [6, 7] and negatively impacting adherence to treatment plans [8]. On the other hand, manifestations of RA disease activity (e.g. recurrent pain, fatigue, prolonged inflammation) themselves act as stressors and influence mental health via changes in cognitive appraisal, affective states, and behavioural coping responses. Several alterations in the stress system of RA patients have been found, e.g. a diminished adrenocorticotropic stress response [9, 10], a shift from β- to α-adrenoreceptors on the surface of immune cells [11–13], impairment in the inflammation-inhibiting capacity of cortisol [14], and a disturbed circadian rhythm [15]. These modifications could potentially result in increased pro-inflammatory responses and a deterioration in rheumatic activity.

In contrast, it has been shown that positive emotional experiences, such as mirthful laughter, were followed by changes in cytokine levels connected with a decrease in pro-inflammatory (TNF-α) levels and an increase in anti-inflammatory activity (IL-6, IL-4, IL-1RA) in RA patients [16]. Furthermore, in patients with systemic autoimmune disorders such as RA and systemic lupus erythematosus (SLE), use of the integrative single-case design - specifically developed for the naturalistic investigation of PNI mechanisms in health and disease - revealed a cyclic response pattern in urinary neopterin (an inflammation marker) following emotionally meaningful positive everyday incidents. This pattern ultimately resulted in decreases in neopterin levels after 3–4 days ([17], unpublished data). Based on these findings, it can be suggested that enhancing coping flexibility among RA patients and incorporating stress management programs into RA treatment may have a positive impact on the disease's outcome [18–21].

In a meta-review, Prothero et al. [18] analysed the effect of psychological interventions in patients with RA (8 reviews; 66 studies; 7279 patients) and found immediate postintervention improvements in various categories, namely, pain, fatigue, depression, anxiety, self-efficacy, coping behaviour, physical ability, and functional disability. These beneficial effects remained evident in follow-up assessments for depression (after 8.5 months), coping behaviour (after 8.5 months), self-efficacy (after 15 months), and physical activity (10–14 months). Disease activity and tender or swollen joints showed a delayed improvement after ten weeks and 8.5 months, possibly caused by mediating effects of the postintervention improvements (e.g. depression, coping). Additionally, it has been demonstrated that psychological interventions, including cognitive-behavioural pain management, emotional expression, and stress management, can influence the levels of stress system parameters associated with the immunopathogenesis of RA, such as IL-6, IFN-γ, cortisol, and IL-8 [19–21].

In this study, a psychotherapeutically guided, group-based intervention program will be conducted with a sample of RA patients over 9 months. This program synergistically combines a dynamic-interactional model with disorder-specific coping-oriented perspectives to improve participants’ social, emotional, and problem-solving competencies. The aim of the study is to evaluate the effect of the intervention program using multimodal data: multiple psychosocial and physiological (immunoendocrine) measurements, scores of RA disease activity, and healthcare-related data. Furthermore, it has been suggested that the complex relationship between a psychological intervention and changes in psychophysiological variables can be better investigated by combining both between- and within-subject data over an extended period [22]. Thus, for each patient, measurements of relevant variables will be conducted at regular intervals over 18 months: once before the intervention, five times during the 9-month intervention period, and three additional times during the 9-month follow-up phase. The control group will not participate in the intervention program, but measurements of variables will be performed according to the same temporal protocol, allowing the analysis of inter- and intrasubject variation.

In addition, integrative single-case studies will be performed on a subset of patients. Specifically, patients in both the treatment and control groups will be closely monitored over the course of approximately 1 month, with assessments taken at 12-h intervals in their everyday life (“life as it is lived”). These assessments will occur once before and once after the intervention and will include close-meshed biological (urine samples), psychological (questionnaires), and social (in-depth interviews) measurements [23]. The high ecological validity of the integrative single-case design with a focus on interview evaluation and analysis of biopsychosocial time series data will allow the real-life investigation of postinterventional changes regarding stress system functioning in RA. By doing so, potential PNI mechanisms mediating or moderating the effects of the intervention could be identified in an exploratory manner.

## Methods

### Study design

This study evaluates the effect of a self-management education program on several indicators of disease activity and associated psychosocial and physiological variables in patients diagnosed with RA and will take place in Bavaria, Germany, from March 2022 to December 2024. Enrolled patients (*n* = 440) will be randomly assigned (randomized) in equal numbers to either an intervention (*n* = 220) or control group (*n* = 220). The intervention group will participate in 15 2-h sessions over nine months in subgroups of 6–12 participants, aimed at enhancing individual health and life skills. The program will be led by psychotherapists who are specifically trained.

The training subgroups will not run simultaneously but will start independently whenever enough patients in a region have enrolled to form an intervention subgroup. To evaluate the effect of this intervention, various indicators of RA disease activity, immune and stress system activity, and psychological condition will be assessed through a set of standardized questionnaires and biochemical analyses of blood, urine, and saliva samples. Outcome variables will be measured at regular intervals before the intervention (baseline), during the 9-month intervention (five time points), and during the 9-month follow-up phase (three time points) at patients’ appointments with their respective rheumatologists. Further data on health-related costs will be acquired through the participating insurance companies (BKK-LV Bayern and AOK Bayern). The subsequent statistical analysis will then assess intra- and interindividual effects based on comparing time points and study groups. Furthermore, a total of ten patients (*n* = 5 from the intervention group, *n* = 5 from the control group) will be investigated thoroughly in integrative single-case studies [21] using biopsychosocial measurements collected at 12-h intervals to produce time-series data for approximately 1 month before and after the intervention. Patients allocated to the control group will receive an expense allowance of 260 Euros to cover the 26 h required for project-related activities during the nine time points of the study (equivalent to ten euros per hour). All patients will continue to receive standard treatment from their rheumatologists during the study. An overview of the study’s timeline can be seen in Fig. 1. No adverse events or harm is expected from the study.

**Fig. 1 Fig1:**
[figure not shown]
Project timeline RT, rheumatologist; PT, psychotherapist; PHQ-9, Patient Health Questionnaire; VAS, visual analogue scale; DAS 28, Disease Activity Score; SDAI, Simplified Disease Activity Score; CDAI, Clinical Disease Activity Score; FFbH, Funktionsfragebogen Hannover; CRP, C-reactive protein; ESR, erythrocyte sedimentation rate; ACPA, anti-citrullinated protein antibody; STAXI-2, State-Trait Anger Expression Inventory-2; TAS-26, Toronto Alexithymia Scale; SF-12, 12-item Short Form Survey; heiQ, Health Education Impact Questionnaire; PSQI, Pittsburgh Sleep Quality Index; NEO-FFI, NEO Five-Factor Inventory; BMI, body mass index; Cytokines, TNF-α, IL-1β, IL-2, IL-2R, IL-6, IL-10, IL-12, IL-13

### Population, recruitment, and allocation

The study population will consist of patients diagnosed with seropositive chronic polyarthritis (ICD-10-Code M05) or another chronic polyarthritis (ICD-10-Code M06) with a minimum age of 18, who are being treated by an eligible rheumatologist in Bavaria and are insured with either BKK-LV Bayern or AOK Bayern. Furthermore, participants need to have sufficient German language skills to complete the questionnaires used by the study. Patients with a diagnosis of fibromyalgia (ICD-10-Code M79.7) will be excluded from the study. The probands will primarily be recruited with the assistance of rheumatologists who practice in the study region and will introduce the study to their patients. Furthermore, the study will be promoted in relevant self-help networks, and some patients who gave prior consent to receive such offers will get a postal notification by BKK-LV Bayern or AOK Bayern. The goal is to enrol 440 probands, who will be randomized in equal proportions into the intervention and control groups (each *n* = 220). Based on simulations using the *lme4* package in *R* [24, 25], this sample should allow the identification of even small effects (*f* = 0.1) with adequate statistical power (1 – *β* > 0.8) while considering a possible drop-out rate of 20%.

Prior to patient enrolment, eligible registered rheumatologists in Bavaria will be contacted and asked to participate in the study. After application and confirmation of participation, the rheumatologists will receive comprehensive instructions on their tasks and responsibilities within the study. In addition, psychotherapists can apply to lead an intervention subgroup. Before the study starts, psychotherapists will be selected from the applicants using an assessment process and receive comprehensive training in the content, background, and implementation of the PETRA intervention program (“train the trainer”).

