### Statistical analyses

A central question in the statistical analyses represents the interaction of the intersubject factor group membership (intervention or control group) and the intrasubject factor time of measurement, i.e. the question of the target variables’ different trajectories in the intervention and control group. For longitudinal data analysis, generalized linear mixed models will be estimated, and due to their flexibility, they can model both normally distributed data and count data as dependent variables. In addition, missing values due to drop-outs are less of a problem for mixed longitudinal models compared to analyses of variance, providing a major advantage in analysing clinical programs. For all outcome variables, covariates will be included in the analyses as potential predictors (e.g. age, personality, gender, the severity of illness at baseline).

In the context of these generalized linear mixed models, quasi-Poisson regressions are the preferred method for modelling healthcare-related costs, which are associated with the predictors through log-link functions. Quasi-Poisson regression is preferred over classic Poisson regression for this project because it also allows modelling overdispersion in count data through an additional variance parameter. Immunoendocrine marker levels, questionnaire data and healthcare-related data with an approximated normal distribution, in turn, can be modelled linearly or estimated according to the divergent distribution with a fitted link function. Comparisons between the intervention and control groups will be directly integrated into the mixed regression models with a dichotomous indicator variable, whereby the influence of other covariates in the comparison can be accounted for. Statistical significance is indicated by a *p* value < 0.05. In addition, the Benjamini–Hochberg method will be applied as a correction procedure to avoid the inflation of type I errors in multiple analyses.

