## Trial status

(Protocol version 5.0, 24th October 2023)

Recruiting started on 1st February 2022 and ended on 30th September 2023. The study successfully enrolled a total of 73 individuals, with 34 participants in the control group (2 withdrawals) and 39 participants in the intervention group (8 withdrawals). As of now, one integrative single-case study has been conducted. Additional integrative single-case studies are pursued.

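### Version 5.0 still states power above 0.8 for f = 0.1 on the basis of 440 patients, although it reports recruitment closed at 73; the power claim no longer describes the trial

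*Protocol article*

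**What the plan says.** Protocol article, Population, recruitment, and allocation: "The goal is to enrol 440 probands, who will be randomized in equal proportions into the intervention and control groups", 220 in each. Citing simulations with lme4 in R, the section concludes that "this sample should allow the identification of even small effects", with f = 0.1, power above 0.8 and an allowance for 20% drop-out. The Abstract and the Study design section repeat 440 as the planned enrolment.

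Protocol article, Trial status (version 5.0, 24 October 2023): "Recruiting started on 1st February 2022 and ended on 30th September 2023". It continues: "The study successfully enrolled a total of 73 individuals", made up of 34 controls with 2 withdrawals and 39 intervention patients with 8 withdrawals.

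The Statistical analyses section names the group-by-time interaction as a central question, sets significance at p < 0.05 and adds a Benjamini–Hochberg correction. The Discussion has one general remark about limited sample size and does not connect it to the shortfall.

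**The concern.** Version 5.0 is dated more than three weeks after recruitment closed. The authors therefore knew the realised size, yet the target and its power stand in the present or future tense, with no label marking them as the original plan and no figure for the sample obtained.

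The risk lies in how the results will be read. Someone who takes the sample-size paragraph at face value will treat a non-significant result as evidence against even a small effect, because the document promises more than 80% power for one. With about one sixth of the planned patients, that inference is unsafe under most plausible readings of the calculation.

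**Working it through.** **Inputs from the protocol article**
- Planned enrolment 440; drop-out 20%; planned completers 440 × 0.8 = 352 (176 per arm).
- Effect f = 0.1; power stated only as greater than 0.8; alpha 0.05 (two-sided assumed).
- Nine measurements, t0 to t8.
- Realised enrolment 34 + 39 = 73, and 73/440 = 16.6% of target.
- Withdrawals 2 + 8 = 10. If these are counted within the 73 (an assumption), 32 + 31 = 63 remain.

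**Step 1: can the stated power be reproduced?** Not exactly. The article does not give the simulation's contrast, variance components or within-patient correlation ρ. I therefore tried several readings, with ρ assumed between 0.3 and 0.7:
- Plain two-group comparison: d = 2f = 0.2, power = Φ(d·√(n₁n₂/(n₁+n₂)) − 1.960).
- Baseline-adjusted comparison: the same, with d divided by √(1 − ρ²).
- Between-group effect over m = 9 visits: noncentral F with λ = f²Nm/(1 + (m − 1)ρ), on 1 and N − 2 df.
- Group-by-time interaction over m visits: noncentral F with λ = f²Nm/(1 − ρ), on m − 1 and (N − 2)(m − 1) df.
- Nine-visit interaction in the partial-eta convention: the same df, with λ = f² × denominator df.

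**Step 2: power for f = 0.1.** Where a row shows a range, it runs from ρ = 0.3 to ρ = 0.7.

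| Reading | N = 440 | N = 352 | N = 73 | N = 63 |
|---|---|---|---|---|
| Plain two-group | 0.56 | 0.47 | 0.13 | 0.12 |
| Baseline-adjusted | 0.59–0.84 | 0.50–0.75 | 0.14–0.22 | 0.13–0.20 |
| Between-group, 9 visits | 0.93–0.69 | 0.86–0.59 | 0.28–0.17 | 0.25–0.15 |
| Interaction, 2 visits | 0.94–>0.99 | 0.89–>0.99 | 0.30–0.59 | 0.26–0.52 |
| Interaction, 9 visits, partial-eta | >0.99 | 0.98 | 0.33 | 0.29 |
| Interaction, 9 visits, ρ = 0.3 | >0.99 | >0.99 | 0.55 | 0.48 |
| Interaction, 9 visits, ρ = 0.5 | >0.99 | >0.99 | 0.73 | 0.65 |
| Interaction, 9 visits, ρ = 0.7 | >0.99 | >0.99 | 0.94 | 0.89 |

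At the planned size, several readings exceed 0.8 and several do not. The claim for 440 can be neither confirmed nor refuted. At the realised size every row except the last is below 0.8.

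**Step 3: detectable effect.** Under a fixed model, the effect detectable at a given power scales with 1/√N:
- 73 patients against 352: √(352/73) = 2.20.
- 63 patients against 352: √(352/63) = 2.36.

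The direct calculations agree. The plain comparison moves from f = 0.149 to 0.353 (ratio 2.37), and the nine-visit interaction at ρ = 0.3 from 0.058 to 0.137 (ratio 2.36).

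The absolute value does depend on the model. At N = 63 and 80% power, the detectable f is 0.35 (plain), 0.34–0.25 (baseline-adjusted), 0.22–0.31 (between-group, 9 visits), 0.21–0.14 (interaction, 2 visits), and 0.14, 0.12 or 0.09 (interaction, 9 visits, ρ = 0.3, 0.5, 0.7). The span is about 0.09 to 0.35.

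**Limits.** These figures ignore clustering in the therapy subgroups of 6–12, the Benjamini–Hochberg step, departures from compound symmetry and further drop-out, all of which would generally lower power. Already 8/39 = 20.5% of the intervention arm had withdrawn.

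**The case against.** The best defence is that the sample-size paragraph is a planning statement conditional on 440 patients. Falling short of a target makes it inapplicable; it does not make it miscalculated. Nothing is concealed either, since the Trial status section gives enrolment and withdrawals by arm. This stands. A reader might infer from the plain two-group figure (0.47 at 352) that the original power was wrong, but the article points to a mixed-model simulation, and other readings comfortably exceed 0.8.

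A second defence is that power may still be adequate. The interaction is the contrast the article itself names, and over nine visits at ρ = 0.7 it keeps 0.89 with 63 patients. This stands as an exception. It needs an omnibus test, compound symmetry and high correlation. Under the same model the planned 352 would detect f of about 0.04, so a sample of 440 justified by f = 0.1 fits it poorly, although power above 0.8 does not rule it out.

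Third, 63 is not an established analysis size. The withdrawals are an interim count, and mixed models can use the visits of patients who later leave. That is why results are shown for both 73 and 63.

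Two stronger readings are tempting:
- One is that power is now 22–25% and the detectable f is 0.22–0.24. At 63, (1.960 + 0.842) × √(63/352) = 1.185 and Φ(1.185 − 1.960) = 0.22; at 73 the result is 0.25. This assumes planned power of exactly 80% on a one-degree-of-freedom contrast. The article says only above 0.8 and does not identify the contrast.
- The other is that the plan is defective because f = 0.1 is tied to no primary contrast and the power statement does not mention Benjamini–Hochberg. An article commonly leaves such details to the full protocol or SAP, and Data Availability says the full protocol can be requested. That the method "will be applied as a correction procedure to avoid the inflation of type I errors in multiple analyses", where false discovery rate control would be the exact description, is mainly a matter of wording.

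**Conclusion.** The point holds as an unreconciled statement, not as an arithmetic error. The article gives a sample size and power that the recruited trial does not deliver, and it offers no replacement. The firm result is relative: for any fixed model, the detectable effect is about 2.2 times (73) to 2.4 times (63) that at the planned 352 completers. The absolute figures are less certain. Power for f = 0.1 is about 0.12 to 0.73 in most readings, with the high-correlation nine-visit interaction the one exception. These values rest on assumed correlations of 0.3 to 0.7, two-sided testing, and withdrawals counted within the 73. The general caveat in the Discussion does not repair the claim, because it neither mentions the shortfall nor qualifies the power.

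**What to change.** 1. In Population, recruitment, and allocation, and wherever 440 is repeated (Abstract, Study design), label 440 and its power as the original target.
2. Rerun the authors' own lme4 simulation at the realised size (73 enrolled, about 63 remaining), and state the contrast and within-patient correlation used.
3. Put the resulting power and detectable effect, or the expected confidence-interval width, in place of the present claim. Do not insert f = 0.22–0.24 as a fixed figure; the number should come from the rerun.
4. State that a non-significant result is not evidence that no small effect exists.

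The cost is some wording and one simulation rerun. The stated power will probably look less favourable. No extra patients are needed.
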